### Measurement of caregiver outcomes

Quality of life: change of the quality of life between discharge home and 6 months, and discharge home and 12 months, measured by Short Form-12 at discharged from hospital to home, 6 and 12 months [37].

Burden: change in burden measured by the Zarit burden scale at 6 and 12 months [38]. Zarit burden inventory licence will be obtained before the first inclusion.

Anxiety and depression scores: change in anxiety and depression scores between discharge home and 6 months, and discharge home and 12 months, measured by the HADS score.

Occupational status: change in professional activity since the patient’s return home (cessation of all professional activity, reduction in working time) in relation to the caregiving situation. Decrease in social and leisure activities since the patient’s return home in relation to the caregiving situation. Satisfaction with the support received upon return home and with information received, measured at 12 months by an ad-hoc questionnair

### Implementation process measurement

Context: elements of the context, external to the intervention, which may have modified the implementation or effect of the intervention. This will be studied using quantitative and qualitative approaches. Quantitative analysis will assess whether the efficacy of intervention differs according to the centre (stroke centre/stroke unit, usual organization of discharge in the unit), patient’s place of residence (rural/urban area), and healthcare density around the patient’s residence. External barriers and facilitators as perceived by the patients, caregivers and the case manager will also be collected during the semi-structured interviews.

Implementation: population reached by the intervention (characteristics of the patients who received the intervention, comparison with the target population), fidelity of intervention compared to the intervention that was planned, including case manager actions collected by the case manager in a logbook, and the use of the Internet information platform by patient (number of connections, duration of use, type of pages consulted). Any adaptations to the intervention will be collected in the semi-structured interviews with patients, caregivers as well as the case manager. Fidelity will be classified into 3 categories: implemented as planned, implemented with adaptations, not implemented.

Impact mechanisms: acceptability by patients, case managers and stroke professionals, strengths and limitations of the intervention, ownership and use of the intervention by patients and their caregivers, unexpected consequences and difficulties encountered by the case manager. These data will be collected by standardized questionnaires and semi-structured interviews among patients, caregivers and the case manager.

### Data collection

Data will be collected from the stroke unit medical charts by external research assistants (from the public health department). For each patient included in the trial, a case report form will be completed with his/her characteristics (age, sex, medical history, comorbidities, treatment, diagnosis, initial stroke severity as assessed by the National Institutes of Health Stroke Scale (NIHSS) at admission, pre-stroke autonomy as assessed by the pre-stroke m-RS).

Patients will be contacted within one week of discharge to home, as well as 6 months and 12 months thereafter for the collection of outcomes. This will be done by telephone [39] by trained research assistants of the study coordinating centre. Research assistants are experienced in stroke patient follow-up by telephone using the standardised scales used for this study. However, training by a stroke neurologist will be conducted before study implementation to ensure standardisation of data collection. Prior to each call, patients will receive the questionnaires by postal or email (or by hand at discharge) so that they can be read and pre-populate the questionnaires prior to the call. Patients will be given the choice of postal or email at inclusion. The data collected are listed in Table 2.

We will precisely detail support received by patients in the control group to describe the usual practices during the study.

### Data management, confidentiality, and dissemination

All information required by the protocol will be recorded in an electronic case report form (eCRF). This eCRF, specific to the study, will be developed by a data manager from the Hospices Civils de Lyon on the Ennov Clinical^®^ software (version 8.2.0).

The data set will be computerised in a coded way, in accordance with the law for data protection and freedom of information (Article L.1121-3 of the French Public Health Code). The study patients will be identified by a unique study inclusion number and by the first initial of their surname and of their given name.

Data should be entered, as soon as they are collected, by the authorised persons (investigator and personnel recorded on the delegation log) and having at their disposal their own login name according to the law for data protection and freedom of information.

Access to the data will be restricted to only the persons participating in the study. Authentication will be made using passwords, which will be regularly changed. The investigators and clinical research assistants of an investigating centre will only have access to the data for their patients and will enter the data directly into the eCRF using a secured website. The investigator will be responsible for the reliability of the data entered and must complete the data as it is obtained during the patient’s follow-up. Throughout the length of the study, the data will be stored in an ISO 27001-certified data centre and backed up daily.

### Sample size

The study will be powered to detect a difference of 15 points in the SIS-Participation score at 6 months of follow-up between the TAU and the intervention group. A 15-point difference between groups in SIS-P score is considered clinically relevant [40]. To detect this difference, 70 patients per group is needed (assuming a common SD of 27 according previous results from the STROKE-69 cohort, power=90%, bilateral alpha level=0.05). Accounting for 20% attrition, we plan to recruit a total of 170 patients.

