**Methods:**

An open parallel-group randomized trial will be conducted in two centres in France. We will recruit 170 adult patients who have had a first confirmed stroke, and were directly discharged home from the stroke unit with a modified Rankin score ≤3. Intervention content will be defined using a user-centred approach involving patients, caregivers, health-care professionals and social workers. Patients randomized to the intervention group will receive telephonic support by a trained case manager and access to an interactive Internet information platform during the 12 months following their return home. Patients randomized to the control group will receive usual care. The primary outcome is patient participation, measured by the “participation” dimension score of the Stroke Impact Scale 6 months after discharge. Secondary outcomes will include, for patients, quality of life, activation, care consumption, as well as physical, mental and social outcomes; and for caregivers, quality of life and burden. Patients will be contacted within one week after discharge, at 6 and 12 months for the outcomes collection. A process evaluation alongside the study is planned.

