### Randomization

Before discharge from hospital, patients will be randomly assigned to one of the 2 groups at a 1:1 ratio. Randomization will be stratified on centre and presence of a caregiver, and will be centrally allocated using the Ennov Clinical® software (version 8.2.0). Allocation sequence will generate by statistician.

Figure 1 presents the study flowchart.

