### Recruitment

The annual number of stays of eligible patients recorded in the two participating centres guarantees the feasibility of this recruitment. In a previous cohort study conducted in these two centres, over 12 months a total of 612 acute strokes were treated in the stroke center and 208 in the stroke unit [28]. Considering that 70% of these patients return directly to their homes following the acute phase, the number of potentially eligible patients would be 574 over 12 months. Recruitment of 170 patients over 12 months, or 15 patients per month, is therefore feasible; this rate of inclusion is also consistent with the case manager’s follow-up who would include 7 to 8 new patients in the intervention group per month over 12 months.

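### The sample size figures do not agree: 170 patients with 20% attrition leave 68 per group, not the 70 per group stated as needed

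*Protocol article*

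**What the plan says.** The Sample size section of the protocol article gives the whole calculation in a few lines. The target is set out as "The study will be powered to detect a difference of 15 points in the SIS-Participation score at 6 months of follow-up". The remaining inputs are "assuming a common SD of 27 according previous results from the STROKE-69 cohort" and "power=90%, bilateral alpha level=0.05". The result is "To detect this difference, 70 patients per group is needed", and the section closes with "Accounting for 20% attrition, we plan to recruit a total of 170 patients".

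The total of 170 appears twice more. The abstract (Methods) says "We will recruit 170 adult patients who have had a first confirmed stroke", and the Recruitment section says "Recruitment of 170 patients over 12 months, or 15 patients per month, is therefore feasible". The Randomization section sets equal allocation: "patients will be randomly assigned to one of the 2 groups at a 1:1 ratio". So 170 recruited means 85 per group, and 70 per group means 140 in total.

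The article does not show how the 20% was turned into 170.

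**The concern.** A sample size paragraph links three numbers: the patients needed for analysis, the proportion expected to be lost, and the patients to recruit. Any two fix the third. Here all three are printed and they do not fit together. If 20% are lost, fewer than 70 per group remain. If 70 per group are to remain, either the loss must be below 20% or more than 170 must be recruited.

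What is at stake is mainly the accuracy of the published justification. Readers will set the final report against this paragraph, comparing the number analysed with 140 and the observed loss with 20%. As printed, the trial could recruit in full, lose exactly the proportion it allowed for, and still fall short of its stated requirement. The effect on power has to be worked out before giving the point any more weight than that.

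**Working it through.** **Inputs** (Sample size and Randomization sections): difference 15 points; common SD 27; power 90%; two-sided alpha 0.05; 70 per group needed; attrition 20%; total recruited 170; allocation 1:1.

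**Step 1. Reproduce the 70 per group.**
- Normal approximation: n per group = 2 × (1.960 + 1.2816)² × 27² / 15² = 68.09, which rounds up to 69.
- Two-sample t test (non-central t): power is 89.97% at 69 per group and 90.4% at 70, so 70 is the smallest size that reaches 90%.

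The stated 70 per group is reproduced exactly by the t test.

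**Step 2. Apply the stated attrition to the stated total.**
- 170 × (1 − 0.20) = 136 in total.
- Per group: 85 × 0.80 = 68.
- Shortfall: 140 − 136 = 4 patients, or 2 per group.

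**Step 3. Work back from the stated requirement.**
- 140 / (1 − 0.20) = 175.
- With equal arms: 70 / 0.80 = 87.5, rounded up to 88, giving 2 × 88 = 176.
- Compared with 170, that is 5 or 6 more patients.

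**Step 4. Find the attrition that 170 can absorb.**
- 1 − 140/170 = 0.176, so 170 keeps 140 only if attrition is at most 17.6%.

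**Step 5. Power at the numbers delivered.**

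| Evaluable per group | t test | Normal approximation |
|---|---|---|
| 68 | 89.5% | 90.0% (89.96%) |
| 69 | 89.97% | 90.4% |
| 70 | 90.4% | 90.8% |

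Going from 70 to 68 per group costs 0.8 to 0.9 of a percentage point, depending on the method.

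**Step 6. Possible routes to 170.**
- 140 × 1.20 = 168, which reaches 170 only with a further rounding up.
- 2 × 68 / 0.80 = 170 exactly, starting from the normal-approximation figure of 68.09 taken as 68.
- 2 × 69 / 0.80 = 172.5, which does not give 170.

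Either of the first two could lie behind the printed total. The article gives nothing with which to choose between them.

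**The case against.** The best defence is that the discrepancy makes almost no difference. By the normal approximation, 68 per group has 90.0% power to one decimal. By the t test it misses the stated level by about half a percentage point. Uncertainty in the assumed SD and in the attrition guess could easily move power by more than that. The difference, SD, alpha, power and 70 per group all reproduce; only the last step is loose. This stands, and it settles the weight of the point.

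A second defence is that 170 may come from a correct division, 68 / 0.80 = 85 per group, with 70 being a separate t-based figure. That is possible, but it does not remove the inconsistency: the printed requirement of 70 would then not be the number behind 170.

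A third is that the Statistical analysis section plans an intention-to-treat primary analysis with imputation where appropriate, so more than 136 patients might enter the model. Imputing missing 6-month scores does not restore the full information of observed ones, and the plan itself chose to inflate for attrition.

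A fourth is that the full protocol may show the working. It may, but the point does not rest on missing detail: the article prints all three numbers, and they disagree.

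A reader might also infer that attrition was mistakenly multiplied on instead of divided out. The article does not support this. Multiplying gives 168, not 170, and the division route from 68 gives 170 exactly.

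**Conclusion.** The point holds as a minor arithmetic inconsistency. At the stated 20% attrition, 170 recruited leave 136 (68 per group), against a stated need of 140 (70 per group). Keeping 140 would take 175 patients, or 176 with equal arms; 170 suffices only if attrition is at most 17.6%. How the mismatch arose is unknown.

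It does not show that the trial is underpowered, although a reader might infer this from the shortfall. Power at 68 per group is 89.5% by the t test, against 90.4% at 70.

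These figures assume that attrition means patients without a 6-month participation score, that losses fall equally on the two arms, and that the article's difference of 15 and SD of 27 are right. The power figures are for an unadjusted two-group comparison.

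**What to change.** Reword the last sentence of the Sample size section so that the three figures agree. Either of these would do:

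- *170 patients allow for about 17.6% attrition while keeping 70 per group.*
- *170 patients leave 68 per group after 20% attrition, giving about 89.5% power (t test).*

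The cost is one sentence; the design, the total of 170 and the recruitment plan stay as they are.

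Keeping both the 70 per group and the 20% would instead mean a target of 176 (88 per group), 6 more patients. The stated pace of 15 per month gives 15 × 12 = 180 in a year, and 88 / 12 = 7.3 new intervention patients per month lies within the 7 to 8 given in the Recruitment section. The gain in power is too small to make this necessary.

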### Recruitment

The annual number of stays of eligible patients recorded in the two participating centres guarantees the feasibility of this recruitment. In a previous cohort study conducted in these two centres, over 12 months a total of 612 acute strokes were treated in the stroke center and 208 in the stroke unit [28]. Considering that 70% of these patients return directly to their homes following the acute phase, the number of potentially eligible patients would be 574 over 12 months. Recruitment of 170 patients over 12 months, or 15 patients per month, is therefore feasible; this rate of inclusion is also consistent with the case manager’s follow-up who would include 7 to 8 new patients in the intervention group per month over 12 months.

### Patient and Public Involvement

The NAVISTROKE study will be conducted in partnership with patient representatives, using different approaches and these at several steps of the study. Patient participation in the study is underpinned by the patient engagement continuum [41, 42]. Two patients from the local stroke patient association (France AVC69) are involved as partners in the research since the first step of the study before grant submission. These two patients are not trained in the science of partnership in research but they have a strong experience of collaboration over several years with our team of researchers and clinicians. They are full members of the study steering committee, and, as such will be involved in decisions throughout the study, in study conduct, in the interpretation of results, and in knowledge transfer activities. The only task they will not be involved in is the recruitment of study participants.

We will also involve a sample of patients (5 to 10) in an advisory committee during the user-centred design phase to define the content of the intervention. Patients will participate in workshops with professionals to give their perspectives regarding the intervention. They will be recruited among volunteers from participants of a previous stroke cohort study [28].

In order to optimize participant engagement in the workshops, we designed a recruitment protocol based on the theory of engagement in social psychology [43] and on the patient partner recruitment guide of the University of Montreal [44]. This protocol consists of four steps: pre-selection by the clinical team; telephone interview; face-to-face interview.

This will allow us to rigorously prepare and inform patients so that the codesign workshops can take place in the best possible way.

### Statistical analysis

Categorical variables will be presented using numbers and percentages, and quantitative variables using mean and standard deviation or median and interquartile range according to their distribution.

Group difference in the SIS Participation domain score at 6 months after hospital discharge will be analysed using a linear model adjusted on the stratification factors (centre and presence or caregiver). The primary analysis will be performed in accordance with the intention-to-treat principle (an imputation method for missing data will be used when appropriate). In a modified intention-to-treat analysis and per-protocol analysis, patients who died before 6 months or those with stroke recurrence before 6 months will be excluded. Change in the SIS participation domain score between 6 and 12 month after discharge will be compared between groups using linear mixed effects model. The model will include patients as random effect, time (6 and 12 months), group (TAU or intervention) and an interaction effect of treatment group × time as fixed effects after controlling for the stratification factors.

Continuous secondary outcomes will be assessed in a similar way. Categorical data will be analysed using logistic or survival models. For non-repeated continuous and binary measurements, ordinary linear regression and logistic or Cox proportional-hazards models will be used when appropriate.

A detailed statistical analysis plan will be made prior to database lock. Analysis and reporting of the results will follow the CONSORT guidelines for reporting randomised controlled trials [45]. Analyses will be conducted using SAS software (version 9.4; SAS Institute Inc., Cary, NC, US). All tests will be two-sided and carried out at the 5% level of significance.

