
## Objectives

The main objective of the trial is to assess the impact of a patient-centred post-stroke transition programme, combining an Internet information platform and telephone follow-up by a case manager, on changes in the level of patient participation, evaluated by the Stroke Impact Scale (SIS), 6 months after their return home compared to usual care. The transition programme aims to empower patients and their caregivers, and help them to identify, understand and use the available medical and medico-social services according to their needs to improve their recovery. Secondary objectives are to study the efficacy of the programme on the following patient-reported outcomes: patients’ level of activation, quality of life, anxiety, depression, fatigue, and sleep quality at 6 and 12 months; on patients’ functional prognosis, attainment of targeted cardiovascular risk factor objectives, healthcare access, as well as occupational and social functioning at 12 months. We will also measure the efficacy of the programme on informal caregivers’ burden, quality of life, anxiety, depression, and occupational and social functioning. A process evaluation of the intervention implementation will be conducted using a mixed-method approach based on the Medical Research Council guidance [17, 18]. Semi-structured interviews will be conducted to understand the barriers and facilitators perceived by patients and the case manager.

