### Setting and patients

The target population is composed of adult acute stroke patients managed in the participating stroke units. In the Rhône county (1,859,524 inhabitants), two stroke units manage acute stroke patients: one stroke centre in the Lyon University neurological hospital, including 12 acute stroke beds, and one stroke unit in a general hospital in the north of department with 6 acute stroke beds. Stroke neurologists will recruit adult patients who have had a first confirmed ischemic or haemorrhagic stroke managed in the participating stroke units, living in the Rhône department, and whose discharge from the stroke unit directly home is planned. The study will include only patients presenting a modified Rankin score (m-RS) of 1 to 3 at discharge from the stroke unit. Patients presenting with aphasia may be included if an informal caregiver is willing to commit to participate in the follow-up with the case manager. Neurologists should inform patients and their caregivers and obtain their consent before their inclusion in the study. Patients already living in an institution prior to stroke, or unable to communicate in the case of absence of informal caregiver or unwillingness to participate in the follow-up will not be included.

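### The primary model is valid, but it names no prognostic baseline covariate although several are available before randomisation, so it may give up precision

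*Protocol article*

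**What the plan says.** Under Statistical analysis, the 6-month SIS participation score "will be analysed using a linear model adjusted on the stratification factors (centre and presence or caregiver"). These are the factors used at allocation: "Randomization will be stratified on centre and presence of a caregiver" (Randomization). The section names no further covariate for this comparison. It does announce a detailed analysis plan before database lock.

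Three patient characteristics fixed before randomisation are on the case report form (Data collection): age, "initial stroke severity as assessed by the National Institutes of Health Stroke Scale (NIHSS) at admission, pre-stroke autonomy as assessed by the pre-stroke m-RS". A fourth, disability at discharge, follows from eligibility: "The study will include only patients presenting a modified Rankin score (m-RS) of 1 to 3 at discharge from the stroke unit" (Setting and patients). Randomisation takes place before discharge.

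Table 2 schedules participation at 6 and 12 months only. The SIS also appears at 1 week, but in the quality-of-life row, and the Secondary outcomes section defines that outcome as the other SIS dimensions. The main objective is nevertheless worded as an effect "on changes in the level of patient participation, evaluated by the Stroke Impact Scale (SIS), 6 months after their return home" (Objectives).

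**The concern.** In a randomised comparison analysed by a linear model, pre-specified adjustment for baseline variables that predict the outcome leaves the target difference unchanged and lowers its variance. It also removes the part of the estimate's random error that comes from chance imbalance in those variables. The usual first choice, the baseline value of the outcome, is not available here because participation is first measured at 6 months. That leaves clinical predictors, which the stated model does not use. At stake is the width of the primary confidence interval, and some power in a trial planned with little margin.

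The missing early measurement also affects the main objective. A change in participation up to 6 months cannot be estimated if nothing is measured before 6 months. The Primary outcome, Sample size and Statistical analysis sections all work with the 6-month score itself.

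**Working it through.** **Inputs from the protocol article.** Difference 15 points, SD 27, two-sided alpha 0.05, power 90%, 70 per group, 20% attrition, 170 recruited (Sample size); 1:1 allocation (Randomization). Evaluable patients per arm after attrition: 170 × 0.8 / 2 = 68.

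**Input not in the documents.** R², the share of outcome variance explained by the added covariates beyond centre and caregiver presence. I use 0 to 0.30 as an assumed range.

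**Step 1: reproduce the plan.** By the normal approximation, n per arm = 2 × (27/15)² × (1.960 + 1.282)² = 68.1, so 69. By the non-central t distribution, power is 89.97% at 69 per arm and 90.4% at 70, so 70 per arm reproduces. The SD of 27 enters with no reduction for covariates.

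**Step 2: unadjusted reference at 68 per arm.** SE = 27 × √(2/68) = 4.63. The t quantile on 134 degrees of freedom is 1.978, so the 95% CI half-width is 1.978 × 4.63 = 9.16 points. Non-central t power for 15 points is 89.5%.

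**Step 3: add covariates.** Residual SD = 27 × √(1 − R²), then the same formulas.

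| Assumed additional R² | Residual SD | SE | 95% CI half-width (points) | Power for 15 points |
|---|---|---|---|---|
| 0 | 27.0 | 4.63 | 9.2 | 89.5% |
| 0.05 | 26.3 | 4.51 | 8.9 | 91.0% |
| 0.10 | 25.6 | 4.39 | 8.7 | 92.4% |
| 0.20 | 24.1 | 4.14 | 8.2 | 94.9% |
| 0.30 | 22.6 | 3.87 | 7.7 | 97.0% |

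Spending about seven further model degrees of freedom changes power by less than 0.1 percentage point, so the extra terms cost almost nothing.

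**Step 4: if the planning inputs are optimistic.** With a true difference of 12 points and SD 27, power is 73% unadjusted, 77% at R² 0.10 and 87% at R² 0.30. With 15 points and SD 30, it is 82%, 86% and 93%.

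**Step 5: availability and timing.** Age, admission NIHSS and pre-stroke mRS are listed in the case report form. Discharge mRS is not in that list, and Table 2 schedules the Rankin score at 12 months only. The evidence for it is the entry criterion. The 1-week SIS is collected after randomisation and discharge, so it is not a baseline variable.

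**The case against.** The strongest reply is that nothing here is wrong. Adjusting for the stratification factors matches the randomisation and gives a valid comparison. The sample size assumes no covariate gain, and the trial has 89.5% power after attrition against a 90% target. A fuller analysis plan is announced and could add covariates. All of this stands, except that the announced plan is only a partial answer: the article already states the primary model, so the point concerns stated text and not missing detail.

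The second reply is that the size of the gain is unsupported. This also stands. No section gives the variance explained by age, NIHSS or mRS. Entry is limited to first strokes discharged directly home with mRS 1 to 3, which narrows the spread of disability and may weaken prediction.

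A reader might infer more than the documents bear out:

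- **That the stated analysis is biased by imbalance.** Under randomisation, chance imbalance is already reflected in the standard error; adjustment removes part of that error.
- **That all four variables are certain to be in the database.** Discharge mRS is evidenced by eligibility only.
- **That the stratification factors carry no information on severity.** Patients with aphasia may enter only if a caregiver commits to the follow-up, and the two centres differ in type, so some link is plausible.
- **That the same covariates belong in every continuous secondary model.** Some of those outcomes are defined as changes from discharge, and some are caregiver outcomes for which the patient's NIHSS may matter little.

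**Conclusion.** The point holds as an avoidable loss of precision in a valid primary model. Its direction is sound; its size is not established. If the added covariates explain 5% to 30% of the variance beyond the stratification factors, power at 68 per arm rises by 1.5 to 7.5 percentage points and the CI half-width shrinks by about 0.2 to 1.5 points. With an R² near zero the gain is negligible, and restricted entry makes the lower end of the range a real possibility. These figures assume SD 27, a 15-point difference and exactly 20% attrition. They do not show that the trial is underpowered.

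Secondarily, the word for change in the main objective does not fit the measurement schedule and should be aligned with the outcome that is analysed.

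**What to change.** Before any outcome data are seen by group, pre-specify the primary linear model as group + centre + caregiver presence + age + admission NIHSS + discharge mRS, with pre-stroke mRS optional. Confirm first that discharge mRS is recorded in the eCRF. Do not use the 1-week SIS as a covariate, because it is measured after randomisation. Choose covariates for the secondary models outcome by outcome.

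Reword the main objective as the between-group difference in the SIS participation score at 6 months.

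The cost is wording in the protocol and analysis plan. No patients or visits are added. No new data are needed, provided that discharge mRS is confirmed as recorded.
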